## **ABSTRACT**

### Context:

Non-invasive ventilation (NIV) can be used in acute respiratory failure to delay and possibly even prevent invasive mechanical ventilation. Through support pressure (Pinsp), NIV can reduce the patient's respiratory effort. Estimation of respiratory effort may be useful to titrate Pinsp to individual requirements. Previous experiments have indicated usefulness of the diaphragm thickening fraction (DTF) for this purpose. Other study groups have proposed that additional assessment of the intercostal muscle thickening fraction (ITF) may further improve this estimation, however this has never been tested during noninvasive ventilation.

### Objectives:

This study aims to test proportions and correlation of DTF and ITF in different respiratory effort conditions induced by exercise load during NIV of healthy volunteers.

### Study Design:

This is a physiological study.

### Setting/Participants:

The study is performed in the I. Medical department.

Healthy volunteers will be recruited for this study.

## **1 BACKGROUND INFORMATION AND RATIONALE**

Non-invasive ventilation (NIV) can be used in acute respiratory failure to avoid invasive mechanical ventilation. By providing supportive pressure, NIV can reduce the patient's respiratory effort. Estimating the respiratory effort can be helpful in adapting ventilation to individual requirements. Studies have shown that inspiratory diaphragmatic thickness (DTF) increase is useful for this purpose. Other study groups have suggested that an additional measurement of intercostal muscles (ITF) could further improve this estimate, but this has never been tested during non-invasive ventilation. The aim of this study is to investigate the respective proportion and correlation of DTF and ITF under different conditions of respiratory effort elicited by exercise during non-invasive ventilation in healthy volunteers.

### **1.1 Compliance Statement**

All investigators will ensure that this trial is conducted in accordance with the principles of the Declaration of Helsinki, relevant regulations, and Good Clinical Practice. The investigators will perform the study in accordance with this protocol. Collection, recording, and reporting of data will be accurate and will ensure the privacy, health, and welfare of research subjects during and after the study.

## **2 STUDY OBJECTIVES**

### **2.1 Primary Objective**

The purpose of the study is to assess whether ITF adds relevant information on respiratory effort measurements during NIV compared to DTF. As a comparator, respiratory effort will be measured using oesophageal pressure swings.

### **2.2 Secondary Objectives**

The secondary objectives are to determine the correlation of DTF, ITF and oesophageal pressure swings and the influence of increased respiratory effort induced by exercise on their relationships. Another secondary objective is to assess the effect of different levels of respiratory support (spontaneous breathing, CPAP, pressure support) on DTF, ITF and oesophageal pressure swings. Furthermore, factors influencing the correlation of DTF, ITF and oesophageal pressure swings should be identified.

### **3 INVESTIGATIONAL PLAN**

#### **3.1 General Schema of Study Design**

This is a single centre physiological study of healthy subjects receiving non-invasive respiratory support.

#### **3.2 Study Duration and Enrolment**

Recruitment will be started when the ethics committee has approved the study protocol and all additional documents i.e. consent form. Over the course of approximately four months all subjects taking part in this project will be enrolled.

#### **3.3 Total Number of Subjects Projected**

The aimed number of included healthy subjects is 50.

##### **3.3.1 Duration of Study Participation**

Each subject's participation will include ultrasonographic measurement of DTF, ITF and oesophageal manometry during a set of NIV modes. Each participant's participation will last 30 Minutes. The entire study is expected to last about four months. A prolonged recruitment period will be discussed when too few participants have been enrolled after the projected time interval.

#### **3.4 Study Population**

##### **3.4.1 Inclusion Criteria**

1. Volunteers aged 18 or older
2. Ability to give written informed consent

##### **3.4.2 Exclusion Criteria**

1. Known bleeding disorder, history of recurrent bleeding or current anticoagulant therapy
2. Allergy to ultrasound gel or external agents containing plastic (NIV mask, gastric tube)
3. Refusal of or medical contraindication to non-invasive ventilation

## **4 STUDY PROCEDURES**

### **4.1 Screening Visit**

At the screening visit, the following points will be evaluated:

Medical History

Current Medication

Informed Consent

Inclusion criteria

Exclusion criteria

### **4.2 Measurement Period**

**Setup** Subjects take part in the study once. Participants will be seated on a semi-recumbent bicycle ergometer during the whole experiment. At the beginning, participants will be asked to determine their ergometry exercise loads to achieve perceived exertion equivalents to Borg scale 10 (fairly light) and 15 (hard). Participants will undergo three sets of 5 study phases each. The order of the study phases will be randomly assigned, but with the same order of phases in each set.

- First set: seated on the ergometer, but resting
- Second set: ergometry with perceived exertion Borg scale 10
- Third set: ergometry with perceived exertion Borg scale 15

As mentioned above, each set is subdivided into an identical order of 5 study phases. The order of phases is randomly assigned prior to the start of the experiment. The 5 different phases are:

- Without connection to a respirator (phase null)
- Connected to a respirator with PEEP and Psupp of 0 cmH2O (phase P0S0)
- Connected to a respirator with PEEP of 5 cmH2O and Psupp of 0 cmH2O (phase P5S0)
- Connected to a respirator with PEEP of 5 cmH2O and Psupp of 5 cmH2O (phase P5S5)
- Connected to a respirator with PEEP of 5 cmH2O and Psupp of 10 cmH2O (phase P5S10)

The DTF, ITF, airway and oesophageal pressures as well as minute volume, blood pressure, heart rate and SpO2 will be recorded at the end of each study phase.

### **4.3 Follow-up**

There is no follow up for this study.

### **4.4 Subject Completion/Withdrawal**

Subjects may withdraw from the study at any time. They may also be discontinued from the study at the discretion of the investigator for lack of adherence to study measurements. The

Investigator may exclude participants from this study to protect the subject for reasons of safety or for administrative reasons. It will be documented whether or not each subject completes the clinical study. If the Investigator becomes aware of any serious, related adverse events after the subject completes or withdraws from the study, they will be recorded in the source documents and on the CRF.

## **5 STATISTICAL CONSIDERATIONS**

### **5.1 Primary Objectives**

The purpose of the study is to assess whether ITF adds relevant information on respiratory effort measurements during NIV compared to DTF. As a comparator, respiratory effort will be measured using oesophageal pressure swings.

### **5.2 Secondary Endpoints**

The secondary objectives are to determine the influence of increased respiratory effort induced by exercise on absolute values of the index tests and their relationships. Another secondary objective is to assess the effect of different levels of respiratory support (spontaneous breathing, CPAP, pressure support) on DTF, ITF and oesophageal pressure swings.

### **5.3 Statistical Methods**

#### **5.3.1 Primary Objective**

Oesophageal pressure swings are used as the comparator for respiratory effort. Correlations with DTF and ITF will be assessed by calculating repeated measures correlation coefficient. Correlations of DTF and ITF will be additionally visualized using clustered box plots.

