#### **5.3.2 Secondary Objectives**

Differences between measurements in the three sets and/or five phases will be compared using the related-samples Friedman's two-way analysis of variance by ranks and visualized by simple box plots according to set/phase.

Subgroup analyses by gender, BMI, and exploratory analysis of factors influencing the correlation of DTF, ITF and the oesophageal pressure fluctuation.

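### The primary analysis in 5.3.1 correlates each index with oesophageal pressure separately, which does not show whether ITF adds information to DTF

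*Protocol*

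**What the plan says.** Sections 2.1 and 5.1 of the Protocol state the same primary objective: to "assess whether ITF adds relevant information on respiratory effort measurements during NIV compared to DTF". The Abstract (Context) and section 1 give the motive. DTF is already regarded as useful, and other groups have suggested that measuring the intercostal muscles as well might improve the estimate.

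Section 5.3.1 fixes the primary method in three sentences:
- The reference: "Oesophageal pressure swings are used as the comparator for respiratory effort".
- The statistic: "Correlations with DTF and ITF will be assessed by calculating repeated measures correlation coefficient".
- The display: "Correlations of DTF and ITF will be additionally visualized using clustered box plots".

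Section 5.3.2 says that sets and phases will be "compared using the related-samples Friedman's two-way analysis of variance by ranks". It adds subgroup analyses by gender and BMI, and an "exploratory analysis of factors influencing the correlation of DTF, ITF and the oesophageal pressure fluctuation".

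The correlations also appear elsewhere. Section 2.2 opens with "The secondary objectives are to determine the correlation of DTF, ITF and oesophageal pressure swings". Section 5.2, the list of secondary endpoints, leaves that item out and keeps the effect of exercise on the index values and on their relationships. The Abstract (Objectives) gives the aim as to "test proportions and correlation of DTF and ITF in different respiratory effort conditions".

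**The concern.** The question is most naturally read as incremental: once DTF is known, does ITF say anything more about effort? A correlation of each index with oesophageal pressure shows how well that index tracks effort alone. It does not show whether the two indices carry the same information. Overlap is plausible here, because exercise and pressure support move effort up and down and both muscles may follow.

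If 5.3.1 is followed as written, ITF could show a clear correlation with oesophageal pressure and be reported as useful although it repeats what DTF already gives. A modest ITF correlation could equally hide a real independent contribution.

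**Working it through.** **Inputs.** From the Protocol: 50 participants (3.3), and three sets of five phases, so 15 measurements each (4.2). Section 5.4 describes the pilot correlation of DTF with oesophageal pressure as moderate and gives no number. It gives no alpha, power or effect size, and says that a formal sample size calculation was not possible, so there is no planned figure to reproduce. All correlations below are assumptions, and so is the two-sided 0.05 level.

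**Notation.** Within participant, r1 = r(DTF, oesophageal pressure), r2 = r(ITF, oesophageal pressure) and r12 = r(DTF, ITF).

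**Gain in explained within-participant variance from adding ITF to DTF:**

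ΔR² = (r1² + r2² − 2·r1·r2·r12)/(1 − r12²) − r1² = (r2 − r1·r12)²/(1 − r12²)

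Section 5.3.1 clearly supplies r1 and r2. The gain also needs r12.

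With r1 = 0.6 and r2 = 0.5:

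| r12 | Substitution | ΔR² |
|---|---|---|
| 0 | 0.50²/1 | 0.25 |
| 0.3 | 0.32²/0.91 | 0.11 |
| 0.5 | 0.20²/0.75 | 0.05 |
| 0.7 | 0.08²/0.51 | 0.01 |
| 0.83 | 0.002²/0.311 | 0.00 |
| 0.95 | (−0.07)²/0.0975 | 0.05 |

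The gain falls to nil near 0.83 and rises again beyond it, so the table illustrates the range and does not bound it.

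**Second set of assumptions.** With r1 = 0.5 and r2 = 0.4, the partial correlation of ITF given DTF is (r2 − r1·r12)/√[(1 − r1²)(1 − r12²)]. A simulation of 50 participants × 15 measurements (1,000 replicates, participant-centred values, independent errors) counted how often each statistic was significant:

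| r12 | Partial r | ΔR² | ITF correlation significant | Partial correlation significant |
|---|---|---|---|---|
| 0.2 | 0.354 | 0.094 | 100% | 100% |
| 0.5 | 0.200 | 0.030 | 100% | 100% |
| 0.8 | 0.000 | 0.000 | 100% | 5% |

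The planned ITF coefficient looks the same in all three rows. Only the joint analysis separates them.

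**Why a p-value alone would not settle relevance.** The within-participant degrees of freedom are 50 × (15 − 1) − 1 = 699. If errors are independent, the correlation detectable with 80% power is tanh[(1.96 + 0.84)/√697] ≈ 0.106. With r1 = 0.6, a partial r of that size is a gain of 0.106² × (1 − 0.36) ≈ 0.007, under one percentage point. The 15 measurements are serial, so independence is the favourable extreme. If each participant counted as a single observation, the figure would be tanh[2.80/√47] ≈ 0.39.

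**The case against.** **The third coefficient may be intended.** The Abstract (Objectives) names the correlation of DTF with ITF, 2.2 speaks of the correlation among all three measures, and the box plots in 5.3.1 are described as additional, which may mean additional to a computed coefficient. Repeated-measures correlation is the correlation of participant-centred values. On complete data, the three coefficients therefore fix the partial correlation and the gain exactly. This stands. A reader might infer that the trial could not answer its primary question in either direction whatever it reports. The documents do not support that, because the answer may be derivable from coefficients that the Protocol arguably implies. What is missing is any plan to derive it, give its uncertainty or judge its size.

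**The comparison may be head-to-head.** The wording of the objective can mean how well ITF tracks effort relative to DTF, and two coefficients address that more directly. This reading is possible, although the background favours the incremental one. Even so, no test or interval for the difference between two dependent correlations is stated.

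**Both indices do appear together.** The box plots may show DTF and ITF side by side, and the exploratory analysis concerns all three measures. So it would be too strong to say that no analysis involves both. Neither, however, is an assessment of what ITF contributes given DTF.

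**A secondary analysis in the primary's place?** Section 2.2 invites that inference. But 5.2 drops the plain correlation item, so section 5 on its own uses correlations consistently for the primary objective. The documents support a disagreement between 2.2 and 5.2 and no more than that.

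**A statistical analysis plan could add a joint model.** It could, and detail left to such a plan is not at issue. The point is that the Protocol names a primary method, and that method does not match the objective above it.

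**Conclusion.** The point holds in this form: the primary method stated in 5.3.1 does not by itself answer the primary objective. The two correlations with oesophageal pressure leave the added value of ITF undetermined. In the illustration it runs from nil to 25 percentage points of within-participant variance for the same two coefficients. The upper end needs DTF and ITF to be uncorrelated, which may be unlikely under a shared manipulation of effort. A span from 0.11 to 0.00 remains for r12 between 0.3 and 0.83.

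That two coefficients are not enough is algebraic and does not depend on the assumed values. The sizes do. The detectable partial correlation near 0.11 also rests on independent errors within participants.

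**What to change.** In 5.3.1, make the contribution of ITF given DTF the primary analysis, by either of:

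- a repeated-measures partial correlation of ITF with oesophageal pressure swing, given DTF; or
- two nested linear mixed models for oesophageal pressure swing with participant random effects, one on participant-centred DTF and one adding participant-centred ITF.

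Report the gain in within-participant R², or the fall in residual SD in cmH2O, with a 95% CI from a bootstrap that resamples participants. Say in advance that relevance is judged on the size of that gain and not on p alone.

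If a head-to-head comparison is what is meant, reword the objective and state an interval for the difference between the two dependent correlations.

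Keep the pairwise correlations, including DTF with ITF, as the secondary analysis that 2.2 names, and bring 5.2 into line with 2.2.

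The cost is a rewording of 5.3.1 and 5.2 and one further analysis. All the measurements are already taken at the end of every phase, so no participants, procedures or data are added.

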### **5.4 Sample Size and Power**

In a previous pilot experiment with 23 participants, we studied the correlation of DTF and oesophageal pressure swings, where we found a moderate correlation and fair discrimination between exercise loads of DTF and oesophageal pressure swings (not yet published). Furthermore, we observed inter-individual differences in the DTF/oesophageal pressure relationship, that might be explained by habitus, BMI or gender. However, the small sample size prevented any meaningful evaluation of this question. No other comparable studies exist for this study question. Formal sample size determination cannot be calculated, the authors conjecture that 50 participants will be needed to adequately control for confounding factors.

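### The primary analysis plans separate within-person correlations for DTF and ITF, which do not measure whether ITF adds information on effort to DTF

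*Protocol*

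**What the plan says.** Protocol section 5.1 (and 2.1) sets the primary objective: to "assess whether ITF adds relevant information on respiratory effort measurements during NIV compared to DTF". The abstract gives the background: other groups propose that "additional assessment of the intercostal muscle thickening fraction (ITF) may further improve this estimation".

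Section 5.3.1 fixes the method. The reference is the oesophageal swing ("Oesophageal pressure swings are used as the comparator for respiratory effort"), and then: "Correlations with DTF and ITF will be assessed by calculating repeated measures correlation coefficient". The only other primary output is graphical: "Correlations of DTF and ITF will be additionally visualized using clustered box plots".

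Section 5.4 reports from a pilot of 23 people that "we observed inter-individual differences in the DTF/oesophageal pressure relationship, that might be explained by habitus, BMI or gender". These differences are taken up among the secondary analyses in section 5.3.2: "Subgroup analyses by gender, BMI, and exploratory analysis of factors influencing the correlation of DTF, ITF and the oesophageal pressure fluctuation". Section 3.3 sets the sample: "The aimed number of included healthy subjects is 50". Section 4.2 gives three sets of five phases, so 3 × 5 = 15 readings per participant and 50 × 15 = 750 in all.

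**The concern.** The objective concerns an increment: what is known about effort from DTF and ITF together that is not known from DTF alone. The planned statistic relates each index to the oesophageal swing separately. Whether ITF adds anything depends also on how far the two indices carry the same signal, and section 5.3.1 does not bring that into any comparison.

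There is a second gap. Repeated-measures correlation gives each participant an own intercept and all participants a common slope. It shows whether an index rises and falls with effort inside a person. It does not show whether a given DTF or ITF reading means the same effort in two different people, and someone reading the index in a new person does not know that person's intercept.

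The primary result could mislead in either direction. A lower coefficient for ITF than for DTF might be read as ITF adding little when the pair predicts effort clearly better than DTF. A high coefficient might be read as showing that an index can be interpreted across people, which it does not test.

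**Working it through.** The plan contains no calculation to reproduce; section 5.4 states that the sample size is a conjecture. The check is partly algebra and partly simulation with assumed inputs.

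**1. Level differences drop out (algebra).** For index x and swing y, person i, reading j:

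r = Σ(x_ij − x̄_i)(y_ij − ȳ_i) / √[Σ(x_ij − x̄_i)² · Σ(y_ij − ȳ_i)²]

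Adding a constant c_i to all of person i's x values moves x̄_i by c_i as well, so every term is unchanged. Numerical check (50 people, 15 readings, effort SD 1, noise SD 1): with person offsets of SD 10 the coefficient is 0.671 before and after. The pooled correlation, which ignores person, falls from 0.677 to 0.092 with offsets of that SD.

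**2. Two coefficients do not fix the increment (algebra).** On person-centred data, with r_D and r_I the coefficients of DTF and ITF with the swing, and r_DI the within-person correlation of DTF with ITF:

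gain in R² from adding ITF = (r_I − r_D·r_DI)² / (1 − r_DI²)

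Take r_D = 0.64 and r_I = 0.50 (illustrative values from the simulation below).

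- If the errors are independent, r_DI = 0.64 × 0.50 = 0.32. The gain is (0.50 − 0.2048)² / (1 − 0.1024) = 0.0871 / 0.8976 = 0.097.
- If r_DI = 0.50 / 0.64 = 0.78, the gain is (0.50 − 0.50)² / (1 − 0.61) = 0.

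The same pair of coefficients fits a useful ITF and a redundant one.

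**3. Simulation.** Assumed, not from the documents: within-person effort SD 1, between-person effort SD 0.7, measurement-error SD 1.2, 400 runs of 50 × 15. DTF = offset + slope × effort + error, with mean slope 1. ITF = 0.7 × effort + error where it is unrelated to the person's DTF offset or slope. Where it compensates, ITF is −offset + 0.7 × effort + error, or (2 − slope) × effort + error. Pooled R² is without participant intercepts.

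| Person differences in DTF | Coefficient DTF / ITF | Within-person R², DTF → DTF+ITF | Pooled R², DTF → DTF+ITF |
|---|---|---|---|
| None | 0.640 / 0.503 | 0.411 → 0.510 | 0.508 → 0.606 |
| Offset SD 1, ITF unrelated | 0.639 / 0.505 | 0.409 → 0.509 | 0.377 → 0.526 |
| Offset SD 1, ITF compensates | 0.639 / 0.503 | 0.409 → 0.509 | 0.374 → 0.600 |
| Offset SD 2, ITF compensates | 0.640 / 0.504 | 0.410 → 0.510 | 0.220 → 0.602 |
| Slope SD 1, ITF unrelated | 0.541 / 0.504 | 0.296 → 0.434 | 0.341 → 0.506 |
| Slope SD 1, ITF compensates | 0.536 / 0.541 | 0.291 → 0.585 | 0.336 → 0.673 |

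- Offsets (rows 1 to 4): the coefficients do not move, while the pooled gain from ITF runs from 0.606 − 0.508 = 0.098 to 0.602 − 0.220 = 0.382.
- Slopes (rows 5 and 6): these are not discarded. With ITF unrelated, the DTF coefficient falls from 0.640 to 0.612 (slope SD 0.5) and 0.541 (slope SD 1). Yet similar pairs of coefficients go with within-person gains of 0.434 − 0.296 = 0.138 and 0.585 − 0.291 = 0.294.

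**4. A model in pressure units.** Assumed: effort 6, 10 and 16 cmH2O by load with shifts for support; DTF = 5 × share × effort + noise (SD 8); ITF = 3 × (1 − share) × effort + noise (SD 4); diaphragm share with mean 0.65. As the between-person SD of the share goes from 0 to 0.15, the cut in prediction error from adding ITF grows from 14% to 19% with participant intercepts kept, and from 14% to 33% for a left-out person. With less noise (SD 5 and 2.5) it grows from 15% to 28% and from 15% to 50%. Under other assumed effort spreads, the left-out figure at share SD 0.15 was 29% to 32%, and 40% to 50% with less noise.

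**The case against.** The strongest reply is that a within-person statistic suits this study. The abstract speaks of adjusting support to the individual, and the design varies load and support inside each participant. This stands as a reason to keep the coefficient. It does not supply the missing comparison, because even within a person two separate coefficients leave the increment open (step 2).

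The objective's wording can also be read as a head-to-head contest between ITF and DTF, for which two coefficients come closer to an answer. But the objective speaks of adding, and the abstract speaks of ITF as an additional assessment that may improve the estimate. The increment is the more natural reading.

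Section 2.2 lists the correlation among DTF, ITF and pressure swings as a secondary objective. If all three within-person coefficients were reported, a reader could apply the formula in step 2. That is a partial answer: section 5.3.1 does not commit to it, and it would still say nothing across people.

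Section 5.3.2 plans gender and BMI subgroups and an exploratory look at other factors, so differences between people are not ignored. As described, those analyses ask what alters the correlation, not whether ITF adds to DTF.

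A separate SAP, which is not shown, may hold a joint model. The point does not rest on missing detail: the protocol names its primary method, and that method does not match its primary question.

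**Conclusion.** The point holds in this form: section 5.3.1 does not measure added information, and its coefficient describes tracking within a person only. The invariance to level differences and the indeterminacy of the increment are algebraic and need no assumption. The collected data stay valid, so this is a change that should be made and not a fatal flaw.

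Three stronger readings are tempting, and the documents do not support them.

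- A reader might infer that the statistic discards all differences between people. It removes differences in level; differences in slope remain in the residual and lower it. Section 5.4 does not say which kind the pilot saw.
- A reader might infer that ITF is meant to correct the pilot's person-to-person differences. The protocol suggests habitus, BMI or gender as explanations and never gives ITF that task.
- A reader might take the simulated gains as expected effects. No input comes from the documents. In the pressure-unit model DTF/5 + ITF/3 equals effort exactly apart from noise, so ITF is built to be nearly a perfect corrector. Part of the gain already appears with participant intercepts kept (19% of error against 33%, or 28% against 50%). That part is missed for want of a joint model, not because level differences are removed.

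**What to change.** Keep the repeated-measures coefficients in section 5.3.1 and label them as within-person tracking. Add a joint comparison of DTF alone against DTF plus ITF for predicting the oesophageal pressure swing, in two versions:

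- **Within person:** participant intercepts kept.
- **Across people:** no participant intercepts, each participant predicted from a model fitted to the others (leave-one-participant-out).

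For each version, report the prediction error in cmH2O with and without ITF, and the difference with a bootstrap interval that resamples whole participants. Copies of a participant drawn more than once should be left out together.

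Possible wording: *The added value of ITF is the reduction in prediction error for the oesophageal pressure swing when ITF is added to DTF, estimated with participant intercepts and, without them, for left-out participants. Repeated-measures correlations describe tracking within a participant.*

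The cost is some protocol text and a little more analysis work. The 15 planned readings per participant suffice, with no change to procedures or sample size. The downside is that across-person figures will look less favourable than the within-person coefficient.
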